### Sample size calculation

In the medical literature, ODS is a critically important outcome, but the incidence of ODS is very low [1, 15, 31]. Therefore, as a surrogate marker of ODS, the rate of overcorrection >12 mmol/L within 24 h or >18 mmol/L within 48 h was calculated for the primary study outcome. A previous study reported that the overcorrection rate was 10–16% with slow continuous correction of hyponatremia [10]. However, there was insufficient information for estimating the rate of overcorrection with intermittent bolus infusion. Based on clinical practice and experience, we estimated that the overcorrection rate was 32% with slow continuous correction during a recent 1-year period. We therefore expect that the rate of overcorrection will be 5% in patients treated with rapid intermittent correction and the rate of overcorrection with slow continuous correction could be as high as 20%. We calculated the required sample size for an estimated dropout rate of 15%, a two-sided level of significance of *α* = 5%, a power of 80%, and found that 89 participants will be required in each group to find a significant difference using a *χ*
^*2*^ test. A total of 178 participants will be included in the analysis. We have considered one interim analysis at the time that a half of subjects complete the study. The O’Brien-Fleming’s alpha spending function will be used to test the first interim and final analysis of primary outcome.

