### Statistical analyses

Statistical analyses will be performed on both per-protocol (PP) and intention-to treat (ITT) bases. For the PP analysis, all participants who completed the study will be included to evaluate the primary and secondary outcomes. For the ITT analysis, all participants who were enrolled and randomized to one of the two groups will be included. The baseline characteristics and laboratory data will be presented as means and standard deviations for continuous variables and as frequencies and percentages for categorical variables.

The incidence of overcorrection, ODS, relowering treatment, and target correction rate (achieved sNa <10 mmol/L within the first 24 h and sNa <18 mmol/L within 48 h) will be compared between the two groups using a *χ*
^*2*^ test and Fisher’s exact test. In interim analysis, if the *P* value < 0.003 then we would stop the study early for significance of outcome. If not, we would recruit another half of subjects. The differences in changes in symptoms and GCS scores between pretreatment and 24 and 48 h, time to reach target sNa, time to achieved sNa ≥5 mmol/L for the first time, and length of hospital stay will be analyzed using Student’s *t* test or the Mann-Whitney *U* test. A value of *P* < 0.05 will be considered statistically significant. All analyses will be performed using SPSS Statistics software V21.0 (IBM Corporation, Armonk, NY, USA).

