A previous study reported that the overcorrection rate was 10–16% in slow continuous correction of hyponatremia [10]. According to unpublished retrospective data in our hospital, overcorrection in the slow continuous correction group occurred in approximately 32% out of 129 hyponatremic patients during a recent 1-year period. Although Moritz et al. reported that there is little or no risk of inadvertent overcorrection [20], data on the rapid intermittent correction regimen were unavailable. We therefore expect that the overcorrection rate will be 5% in patients treated with rapid intermittent correction, and the overcorrection rate in slow continuous correction could be as high as 20%. For this reason, we will plan to perform an interim analysis, which will be conducted after a number of patients equal to half the estimated total sample size have been enrolled. No previous studies addressing differences in efficacy between rapid intermittent correction groups and slow continuous correction groups in each stratification group have been reported. In the interim analysis, we will also examine the ratio of stratification (moderately severe versus severe) for each experimental therapy group and analyze the efficacy of rapid intermittent correction compared to slow continuous correction for each level of stratification. After the interim analysis, the total study population of 178 patients will be adjusted to the ratio of stratification in the experimental therapy groups. In the interim analysis, if the *P* value < 0.003 then we will stop the study early for significance of outcome. If not, we will recruit another half of subjects.

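### The Discussion adjusts the 178 patients after a by-stratum interim comparison of the arms, which conflicts with the fixed stop-or-continue rule and leaves open whether observed effects may shape the second half

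*Protocol article*

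**What the plan says.** The Sample size calculation section sets 89 patients per arm (178 in total) and one interim analysis at half the subjects. O'Brien-Fleming alpha spending applies to the interim and final tests of the primary outcome. The Statistical analyses section stops the trial early if the interim P value is below 0.003 and otherwise continues: "If not, we would recruit another half of subjects".

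The Discussion adds two things to that look. The team will examine the ratio of moderately severe to severe patients in each arm, and will "analyze the efficacy of rapid intermittent correction compared to slow continuous correction for each level of stratification". The next sentence reads: "After the interim analysis, the total study population of 178 patients will be adjusted to the ratio of stratification in the experimental therapy groups". The Discussion then repeats the rule of stopping at P < 0.003 or recruiting the other half.

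The Randomization section allocates 1:1 in blocks of 2, stratified by symptom severity.

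**The concern.** A second half of fixed size and an adjusted population of 178 are different designs, and the article states both. The adjustment is worded as certain. It follows a comparison by arm within strata, so whoever makes it has seen comparative results. The sentence can be read as changing the total, the stratum quotas or the weights.

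Alpha spending allows for testing the primary outcome twice. It does not allow for choosing the size of the second half after seeing how large the effect is. Two things are therefore at stake:

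- **Type I error**, if the size of the second half could respond to the observed effects.
- **Interpretation**, if only the severity mix changes. The planned primary comparison pools the strata, so its rates would then apply to a mix fixed mid-trial by quota and not to the mix of patients presenting.

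**Working it through.** **1. Reproduce the planned figures.** Inputs from the Sample size calculation section: 20% versus 5% overcorrection, two-sided 0.05, power 80%, dropout 15%.

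- Pooled-variance formula without continuity correction, mean rate 0.125: n = [1.960·√(2·0.125·0.875) + 0.842·√(0.20·0.80 + 0.05·0.95)]² / 0.15² = (0.9167 + 0.3834)² / 0.0225 = 75.12 per arm.
- With dropout: 75.12 / 0.85 = 88.4, rounded up to 89. This matches the plan.
- Interim threshold, O'Brien-Fleming-type spending with 0.025 per tail at half information: 4·[1 − Φ(2.2414/√0.5)] = 4·[1 − Φ(3.170)] = 0.00305. This matches P < 0.003.
- With z = 2.968 at the interim (P = 0.003), an overall level of 0.05 requires z = 1.968 at the end, a nominal P of 0.0490.

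The fixed design is therefore coherent, and the question is what the adjustment does to it. Below, k is the size of the second half relative to the first, so k = 1 is the plan. The document gives no range for k; every range used here is an assumption.

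**2. Only the mix changes, total stays 178.** Under the null hypothesis the pooled statistic keeps its distribution. Simulation (400,000 runs) gives 0.0498 and 0.0502 with an assumed severe share of 25% and 50%, that is 0.050.

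**3. Size follows the baseline ratio only.** k is then independent of the observed effect, and the interim falls at information fraction t = 1/(1 + k). With the boundaries left at 0.003 and 0.0490:

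| k | t | Overall two-sided type I error |
|---|---|---|
| 0.5 | 0.667 | 0.0494 |
| 1 | 0.500 | 0.0500 |
| 1.5 | 0.400 | 0.0504 |
| 2 | 0.333 | 0.0507 |

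Recomputing the final boundary at the actual t restores 0.05.

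**4. Size is chosen from the observed effect, worst case.** Given the interim value z₁, the final statistic is (z₁ + √k·z₂)/√(1 + k). Its null probability of exceeding 1.968 in either direction is

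Φ[(z₁ − 1.968·√(1 + k))/√k] + Φ[(−z₁ − 1.968·√(1 + k))/√k].

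Take the largest value over the allowed k at each z₁, integrate over |z₁| < 2.968 with the standard normal density, and add 0.003 for early stopping.

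| Allowed k | Worst-case two-sided type I error |
|---|---|
| 1 to 1.5 | 0.0546 |
| 1 to 3 | 0.0618 |
| 0.25 to 1.5 | 0.068 |
| 0.25 to 3 | 0.076 |

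The mechanism shows at z₁ = 2.5: the null chance of final rejection is 0.39 at k = 1 but 0.73 at k = 0.25. Cutting the second half short after a strong interim result would preserve a chance finding.

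**The case against.** A reader might infer that the plan commits to an effect-driven redesign and that type I error is therefore uncontrolled. The document does not support that. The sentence names its driver, the severity ratio, which is a baseline stratification factor. The efficacy comparison by stratum stands in the preceding sentence, but nothing says that it feeds the adjustment. On the stated driver the error rate stays at 4.9% to 5.1%, so a change in size does not by itself break the level of the final test. The larger figures are bounds: they need the size to be picked at every interim value so as to maximise rejection, over ranges that the document does not contain. Nothing in the Discussion suggests shrinking the second half to a quarter. All of this stands.

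It can also be said that the repeated commitment to recruit the other half makes an unchanged total the likelier meaning, and that the aim may be adequate numbers in each stratum. Both are plausible. Arm balance would not be a reason, since randomization already secures it within strata. A change of mix leaves the within-stratum comparisons valid and affects only the severity mix that the pooled rates describe.

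Finally, a condensed article may leave the detailed rule to the full protocol or analysis plan. That is fair for the missing detail. It does not remove the conflict, because the article itself states both an adjustment and a fixed second half, and attaches the adjustment to a comparative look.

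**Conclusion.** The point holds in a limited form. The adjustment sentence conflicts with the fixed continuation rule in the Statistical analyses section and in the Discussion. It is placed after a comparison of the arms by stratum, with nothing to keep the observed effects out of the decision.

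Under the stated driver the consequence for type I error is negligible; what may change is the severity mix to which the pooled overcorrection rates apply. Only if stratum effects influenced the second-half size would the error rise, to at most about 5.5% to 6.2% with increases only and 6.8% to 7.6% if reductions were also possible. Those bounds assume final testing at 0.0490 and the size ranges shown. This is a cheap improvement that closes an avoidable route to bias; it does not show that the trial's error rate is uncontrolled.

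**What to change.** - Delete the adjustment sentence from the Discussion.
- State that 178 stays fixed and that enrolment after the interim is consecutive, with no severity quota.
- Limit the interim comparison of arms to the primary outcome at P < 0.003.
- Move the stratum-specific comparisons to the final analysis, reported as a treatment-by-severity interaction.

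If an adjustment is to be kept, say what is adjusted and by what rule, base it only on arm-masked data (the severity ratio or the pooled event rate), and recompute the final boundary at the actual information fraction.

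The cost is a small text change. The trial gives up an early stratum-specific comparison and any mid-course change of the severity mix.

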### Trial status

This trial started recruiting in August 2016. Recruitment is expected to conclude by July 2018.

## Abbreviations

ACTH: Rapid adrenocorticotropic hormone
CKD EPI: Chronic Kidney Disease Epidemiology
eGFR: Estimated glomerular filtration
GCS: Glasgow Coma Scale
ICD: *International Classification of Diseases*
ITT: Intention-to-treat
MRI: Magnetic resonance imaging
ODS: Osmotic demyelination syndrome
PP: Per-protocol
SCr: Serum creatinine
sNa: Serum sodium
SPIRIT: Standard Protocol Items: Recommendations for Interventional Trials
TFT: Thyroid function test
